## Abstract

**Background:**

Caring for a person with progressive cancer creates challenges for caregivers. However the needs of caregivers are often not assessed or recognised by health care providers. Research is also lacking in this area, with little knowledge relating to effective strategies to address the specific needs of caregivers. This paper outlines a study protocol aimed at developing and evaluating the effectiveness of a general practice-based intervention to better meet the needs of caregivers of patients with advanced cancer.

**Methods/Design:**

Two hundred and sixty caregivers will be randomised into each of two arms of the intervention (520 participants in total) through patients with advanced cancer attending medical and radiation oncology outpatient clinics at two tertiary hospital sites. Consenting caregivers will be followed up for six months, and telephone surveyed at baseline, 1, 3 and 6 months following their entry into the study or until the patient's death, whichever occurs first. Assessment and management of the unmet needs of caregivers in the intervention arm will be facilitated through a specifically developed general practice-based strategy; caregivers in the control group will receive usual care. Qualitative interviews will be conducted with a sample of up to 20 caregivers and 10 GPs at the conclusion of their participation, to explore their views regarding the usefulness of the intervention.

**Discussion:**

This study will determine whether systematic assessment of caregiver needs supported by caregiver-specific information for General Practitioners is effective in alleviating the unmet needs experienced by caregivers caring for patients with advanced cancer.

**Trial registration number:**

ISRCTN: ISRCTN43614355

## Background

As our ageing population increases, so too does our reliance on the support and care provided by informal caregivers. In 2001, 12.5% of the Australian population was aged over 65, and this is estimated to rise to 25% by 2052 [1]. The number of people with a chronic or life-threatening disease will increase and with it, the absolute numbers of patients requiring palliative care (PC). Although 80% of patients express a wish to die at home, only a third actually do so [2]. However, 90% of patient care in the final year of life occurs at home [3], with many patients moving to an inpatient setting in the final days of life. Hence, much of the burden of care giving is managed in the community, with the greatest burden falling on primary caregivers [4]. Cancer is one of the 10 most common health conditions in receipt of informal care giving in Australia. Care may be equivalent to a full-time job, with 20% of caregivers providing full-time or constant care [5].

Caring for a patient with PC needs carries a number of implications. It is often provided by people who are themselves elderly and/or ill, and care giving may exacerbate the illness burden. Caregivers of patients receiving PC have lower quality of life (QoL-impairment in physical functioning, general health, and vitality) and worse overall physical health than caregivers of patients receiving curative or active treatment [6]. As patients deteriorate physically, caregiver QoL worsens, suggesting a greater need for support at this time [7]. Furthermore, whilst many caregivers feel positively about care giving and derive deep satisfaction in this role, caregivers may also experience a number of physical and psychosocial issues, including reduced social contact, significant financial burden, sadness, anger or resentment which may increase the risk of psychiatric morbidity and complicated grief [4]. Additionally, caregivers report a number of unmet needs across a variety of areas, including: information, communication, and support from services [8]. Family members whose own needs are not identified and addressed early have greater needs, less trust of and confidence in the health care system, and cope more poorly in the later stages, than families who have been informed and supported throughout the course of the illness [9].

However, despite the shift to include family members and primary caregivers as active components in PC [10], it is still common that the primary focus of the caregiver and of health professionals is on the needs and comfort of the patient, meaning that caregiver needs and distress may be considered secondary to the patient's and may be overlooked [11]. For example, in 2003/4, the patient was the client in 98.3% of referrals to Home and Community Care services, yet caregivers are a target group of that program [12]. It has also been suggested that caregivers may be reluctant to raise their own needs with their health care provider, as they do not wish to put their own issues before the patient's or bother the health care professional [13]. On the other hand, health care professionals are often working under tight time restraints, with the average Australian general practice consultation lasting only 14.6 minutes [14], making it difficult to assess both the patient and caregivers needs in one appointment.

Although international literature highlights GPs' variable levels of knowledge about PC and symptom control [15] and their lower perceived levels of competence in these areas compared to specialist PC services, GPs are in an optimal position to evaluate and assess the needs of caregivers. GPs are usually the first point of contact for patients and their caregivers and generally have an established relationship with the patients with palliative care needs as well as having an important contextual knowledge of the family and of the illness. Canadian research indicates that palliative care patients with a regular GP are less likely to seek care from emergency departments [16], and are less likely to die in hospital [17].

Regardless of our knowledge as to the importance of evaluating and addressing caregiver needs and the optimal position that GPs hold for doing this, there is a lack of research investigating the most effective strategies to meet the needs of caregivers. A systematic review of interventions designed to alleviate caregiver burden found only nine such studies [18]. Interventions reported included home care, home respite services, nurse practical and emotional support, and group support, with no reported interventions based in general practice.

Considering the past evidence and lack of research aimed at addressing the unmet needs of caregivers, we will be implementing an intervention which focuses specifically on the needs of caregivers, using GPs as the point of intervention. Specifically, we propose conducting a randomized control trial (RCT), which utilises a GP Caregiver Needs Toolkit (hereafter referred to as the GP Toolkit). The GP Toolkit will contain two resources, which will assist GPs in systematically identifying and addressing the unmet needs of caregivers. The proposed study will build on existing work aimed to improve needs-based PC, and will include a) developing and evaluating the effectiveness of a general practice-based intervention to better meet the needs of caregivers caring for patients with advanced cancer; and b) assessing the efficacy of the intervention in reducing caregivers' reported number and levels of unmet needs when compared to usual care.

### Study aims and hypotheses

The overall aims of the proposed study are to:

1. Use randomized controlled methods to assess the efficacy of the systematic utilisation of a GP Toolkit in reducing caregivers' reported number and level of unmet needs.

2. Evaluate the acceptability of the intervention for GPs and caregivers.

For the proposed study it is hypothesised that the number and levels of unmet needs of caregivers of patients with advanced cancer will be significantly lower in caregivers whose needs are systematically assessed using a needs assessment tool and then addressed by their GP, compared with caregivers receiving usual care.

## Methods/Design

### Study design

The proposed study will use a mixed methods design comprising a RCT and a qualitative evaluation. Participating caregivers will be surveyed using a Computer Assisted Telephone Interview (CATI) at baseline, 1, 3 and 6 months from entry into the study, or until the patient's death, if this occurs first. Assessment and management of the unmet needs of caregivers in the intervention arm will be facilitated through the utilisation of the GP Toolkit resources by both the caregiver and GP following their entry into the study and at 3 months, while the caregivers in the control group will receive usual care. Ethics approval has been obtained from The University of Queensland and Princess Alexandra Hospital (Queensland), and the University of Newcastle (New South Wales). All participants will provide voluntary written consent.

### Setting

The foundation of the Australian health system rests on primary care delivered by GPs who accept unreferred patients and are the first point of contact for most health care problems including prevention and health promotion activities. Over time, the GP builds up a comprehensive knowledge of their patients' medical and psychosocial circumstances, and that of their family. Approximately 80% of all Australians visit a GP at least once per annum. In 2002-03, the Australian population of approximately 20 million people generated 89,832,327 unreferred attendances, ie approximately 4.5 per person per annum [19]. Should specialist medical or allied health services be required, GPs are usually responsible for referring the patient appropriately. This arrangement is funded by a government administered universal health insurance system, which supports a fee-for-service remuneration structure. In 1999, the Australian Government instituted a second form of funding, which encouraged more comprehensive care planning for patients with complex health problems or chronic diseases. This Program, the Enhanced Primary Care (EPC) Program [20], encompasses a range of initiatives that encourage multidisciplinary assessment and management of these problems, and are the basis of the intervention below.

### Participants

### Sample and recruitment

A consecutive sample of caregiver participants will be recruited through Medical and Radiation Oncology services at two major tertiary hospital sites in Brisbane, Australia, in liaison with clinic personnel. These sites provide oncology services to approximately 2.5 million people in southern Queensland, Australia. There are approximately 2,200 GPs in this region. To be eligible to participate in the proposed study, caregivers must: (1) be a nominated caregiver of a patient with a diagnosis of advanced cancer (i.e. cancer that is no longer amenable to cure, with either extensive local or regional spread or metastatic disease); (2) be aged 18 years or older; (3) live within the greater Brisbane area (population approximately 2.0 million); and (4) be able to understand English sufficiently to complete questionnaires and telephone interviews. For practical reasons, the recruitment procedures will be adapted to suit the two recruitment sites. At one site, potentially eligible caregivers of patients attending oncology services will be identified by trained and experienced project personnel who will explain the study to them. Interested caregivers will be offered a flier with a brief overview of the study in plain language, and will be invited to ask the patient's doctor to confirm their eligibility on the flier. The eligibility criteria will be discreetly displayed for reference in each consulting room. Interested and eligible caregivers will be given an information pack to read and will be asked for their contact details for follow-up a week later by a project staff member, to answer any questions and ascertain their response. The information pack will inform caregivers about the study and invite them to return a signed consent form. At the second site, the Clinical Trials Co-ordinator will identify eligible caregivers in liaison with other clinic personnel, and will approach these caregivers to explain the study in plain language. Those who are eligible and interested will be offered the information pack to read, and will be followed up a week later by the Co-ordinator or a project staff member to answer any questions and ascertain their response.

GPs nominated by participating caregivers in the intervention group will be approached by research staff, who will inform them that their patient has agreed to participate, and seeking their willingness to participate.

### Randomization

Upon receiving the signed consent form, one project staff member will randomly allocate participating caregivers into the intervention or control group if their usual GP does not already have a caregiver patient in the study. Randomization will be conducted off-site using computer-generated random number tables and permuted block randomisation with blocks of four participants. However, if the caregiver's usual GP already has patients in the study, s/he will be allocated to that GP's study group, to minimise contamination between the two study arms. The risk of contamination is because the GPs of caregivers randomized to the intervention group have access to several interventions aimed at supporting the caregiver. (See *Intervention *below) There is therefore a high probability that a subsequent caregiver of that GP, randomized to the usual care group, will be offered different care to a caregiver of a GP who has not received training. Based on a previous study of similar populations, we expect that most GPs will have only one participant, and clustering will be minimal [21,22]

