### Procedure

All participating caregivers will be mailed a copy of the CATI survey questions on entry to the study, for reference during the CATI phone calls. These interviews will be conducted by trained and experienced personnel, who will be blinded to the group assignment of participants. CATI data will be collected from control and intervention group caregivers at the same four time points. Baseline CATIs occur before the intervention group caregivers consult the GP. Apart from these interviews, the control group will not be subject to any further intervention from the project.

Intervention group caregivers will also receive a triplicate copy of the NAT-C, with a covering letter to explain the purpose of the NAT-C, to ask caregivers to complete this form and to attend their GP with the completed form as soon as practicable to discuss their needs, with a target of between one and two weeks to allow the GP to first receive an educational visit. At three months following entry into the study, intervention group caregivers will be asked to complete a second NAT-C and discuss it with their GP, to identify and deal with changing needs as the patient's disease progresses.

GPs of the intervention caregivers will be individually visited once by research staff as soon as possible after participant recruitment and allocation to the intervention group, to explain the use of all elements of the GP Toolkit. The research team will follow up GPs by phone to provide any further support required and to ensure the intervention is fully implemented. The frequency of these calls will be tailored to the needs of individual GPs. GPs with more than one caregiver participant will receive a visit only after the first participant is recruited. GPs will be encouraged to use the NAT-C as a guide to discussing the needs nominated by the caregiver, and to planning a course of action. There are no prescribed interventions for given identified needs. Any agreed actions are entirely up to the treating doctor and the caregiver.

Intervention patients who choose not to complete a NAT-C will still be encouraged to visit their GP, who may also choose to use the copy of the NAT-C in the GP Toolkit to guide the discussion, or not. The GP and the caregiver may choose to complete the NAT-C together.

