## Discussion

There are several features of this study design, which take into account the unique challenges inherent in achieving adequate sample size in this difficult population and for a general practice intervention. The first is that recruitment has to be multi-site to achieve the required sample size, which requires collaboration between university-based investigators and groups of clinicians with different work practices. This requires differing recruitment methods being utilised at different sites. We believe this will not lead to recruitment bias because randomisation is a blinded process conducted off site from the recruiting hospitals. Any systematic differences in the patients recruited from the different sites will be distributed evenly between intervention and control groups.

Secondly, we have elected to break randomisation for subsequent patients of a participating GP. Allowing the one GP to treat both intervention and control patients would risk significant contamination and based on our previous experience [21,22], it is not feasible to recruit and randomise one patient per GP with the time and funding available to us through this grant. The randomisation procedure will ensure an even distribution of GPs with more than one patient in each group, minimising the impact of this variation in methods.

Thirdly, we are recruiting through oncology units, even though the intervention will take place in community general practices. This applies a very important principle in general practice-based research, which differs from specialty-based research. When the subjects of the research have a low prevalence condition, it is more feasible to recruit them from situations where the condition is prevalent, then recruit the GPs through the consenting participants. Asking GPs who constantly see a range of undifferentiated problems and many patients per day to recruit people with conditions they may see only a few times per annum is impractical. They are likely to forget that they are participating in the study and miss recruitment opportunities. This method was piloted by GM, and was successfully applied in a similar RCT of palliative care patients [21,22].

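### A fixed, published block size of four leaves, at worst, one third of list-randomised allocations deducible by anyone who sees the running sequence

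*Protocol article*

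**What the plan says.** The Randomization section of the protocol article states that "Randomization will be conducted off-site using computer-generated random number tables" and "permuted block randomisation with blocks of four participants". No variation in block size and no stratification by site is mentioned. The allocator is a member of the project: "Upon receiving the signed consent form, one project staff member will randomly allocate participating caregivers into the intervention or control group". That applies only to a caregiver whose GP has no caregiver in the study yet; later caregivers of the same GP take that GP's arm.

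On recruitment, the Sample and recruitment section says that at one site potentially eligible caregivers are "identified by trained and experienced project personnel who will explain the study to them", and a project staff member contacts them about a week later. At the second site a Clinical Trials Co-ordinator makes the approach, and the later contact is by the Co-ordinator or project staff.

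On who learns the arm, the Procedure section says that "GPs of the intervention caregivers will be individually visited once by research staff", and that intervention caregivers are sent the needs checklist. The telephone interviewers who collect outcomes are blinded. The Discussion rests its case against recruitment bias on the statement that "randomisation is a blinded process conducted off site from the recruiting hospitals".

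**The concern.** With a constant block of four and equal allocation, each block holds two places per arm. Once two places of one arm are used, the rest of the block is known. An observer needs the block length, which is stated, and the earlier allocations, which part of the project team must learn in order to deliver the intervention.

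The stated safeguards address other risks. Being off site from the hospitals keeps the list from clinic staff, but does not by itself keep past allocations from the project's own recruiters. Allocating after the signed form prevents a known assignment from being reversed. It does not prevent someone who can foresee the next assignment from encouraging one caregiver more than another, or from influencing when a form is processed.

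The stake is selection bias. The primary outcome is caregivers' self-reported unmet need, so a recruiter who favoured one arm for caregivers with visibly greater need could unbalance the very quantity being compared.

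**Working it through.** The article gives no figure for predictability, so there is none of its own to reproduce.

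**Inputs.** Block size four (Randomization). Equal allocation, 260 per arm and 520 in total (Abstract). About 330 GPs (Sample size and statistical analysis). Assumption: each GP contributes exactly one list-randomised caregiver, so about 330 allocations come from the list.

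**Certain allocations.** There are six equally likely blocks.
- AABB and BBAA: the third and fourth places are certain, 2 each.
- ABAB, ABBA, BAAB and BABA: only the fourth place is certain, 1 each.

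Mean per block = (2 × 2 + 4 × 1) / 6 = 8/6 = 1.33 of 4 places, or 33.3%. A single block ranges from 25% to 50%; one third is the long-run average.

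**Best guess.** With a and c places left in the two arms, the best guess is right with probability max(a, c) / (a + c).
- Place 1: 1/2.
- Place 2: 2/3.
- Place 3: (1/3) × 1 + (2/3) × 1/2 = 2/3.
- Place 4: 1.

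Average = (0.500 + 0.667 + 0.667 + 1.000) / 4 = 70.8%, against 50% with no information.

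**Scale in this trial.** 330 / 3 = 110 certain allocations; 110 / 520 = 21% of all caregivers. The other 520 − 330 = 190 (36.5%) follow their GP's existing arm and do not draw on the list.

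**Alternatives.** The same enumeration was done for fixed sizes of six and eight. For mixed sizes, lists of 330 were simulated with sizes drawn at equal probability. The observer was given every past allocation and the set of possible sizes, but not the size of the current block.

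| Block sizes | Certain | Best guess correct |
|---|---|---|
| Fixed 4 | 33.3% | 70.8% |
| Fixed 6 | 25.0% | 68.3% |
| Fixed 8 | 20.0% | 66.6% |
| Random 4/6 | about 5.5% | about 69.3% |
| Random 4/6/8 | about 2.3% | about 68.1% |

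Varying the size removes nearly all the certainty but only 70.8 − 68.1 = 2.7 percentage points of guessing accuracy. An observer without knowledge of earlier allocations gains nothing under any of these schemes.

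**The case against.** The strongest reply is that the article does not place any one person in both roles. It names a single allocator working off site, describes recruiters and GP visitors separately, and gives the second site's Co-ordinator no part in allocation or GP visits. A reader might infer that the staff who recruit are the staff who see allocations. The text supports this only for the project team as a body; it neither says that the individuals overlap nor that they are kept apart. Role separation may be set out in a fuller document that is not shown.

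A reader might also infer that a third of all 520 allocations are predictable. They are not: only the first caregiver of each GP draws on the list. The observer would also have to know which earlier caregivers came from the list, where each block starts, and the allocations from both sites. List order follows the arrival of signed forms, which a recruiter cannot fully foresee. This stands, and makes one third a worst case.

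A third reply concerns harm. Sampling is meant to be consecutive, outcome interviewers are blinded, need is measured at baseline, and the models include confounders. These limit the damage, so it would go too far to say that the primary outcome is biased. They do not remove the risk: blinded interviewing protects outcome collection, not enrolment, and the baseline interview is stated to precede the GP consultation, not the allocation.

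Finally, blocks of four are conventional and nothing here is contradictory. That is fair, and it is why the point is an improvement and not an error.

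**Conclusion.** The point holds as a low-severity design improvement. A constant, disclosed block of four in a trial with open treatment makes, on average, one third of list-randomised allocations certain and 71% guessable for an observer who knows the running sequence and the block boundaries. That is about 110 of roughly 330, or 21% of 520, assuming one list-randomised caregiver per GP.

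The figures are a ceiling on average predictability, not an estimate of what would happen. They fall if a recruiter sees only one site's allocations from what appears to be a shared list, and vanish if recruiters see none. The documents do not show that any recruiter has this knowledge, or that selection would follow. What they do show is that the safeguards described in the article would not prevent it.

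**What to change.** Generate the list with block sizes varied at random, for example 4, 6 and 8, and do not disclose them. Have the list and the running allocations held by existing staff who have no role in approaching caregivers or following them up for consent, and say so in the Randomization section. The second step matters more, because mixed sizes alone still leave about 68% of allocations guessable to someone who sees the sequence.

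The cost is regenerating the list, rewording the sentence on block size and adding a statement on who may see allocations. The drawback is a possible imbalance of a few caregivers if recruitment ends inside a block: at most half the block, so 4 with a block of eight against 2 with a block of four.

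The change does not affect later caregivers who take their GP's existing arm. Their allocation is known in advance to anyone who knows that arm, whatever the block size.
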